# Effectiveness of a brief psychological mindfulness-based intervention for the treatment of depression in primary care: study protocol for a randomized controlled clinical trial

**DOI:** 10.1186/s12888-019-2298-x

**Published:** 2019-10-16

**Keywords:** Depression, primary care, Mindfulness-based intervention, Low-intensity, Face-to-face, Internet delivered, Randomized controlled trial

## Abstract

**Background:**

Depressive symptoms are quite prevalent in Primary Care (PC) settings. The treatment as usual (TAU) in PC is pharmacotherapy, despite the high relapse rates it produces. Many patients would prefer psychotherapy, but specialized services are overloaded. Studies that apply Mindfulness-Based Interventions (MBIs) for the treatment of depression have obtained significant improvements. Brief low-intensity approaches delivered from PC could be a promising approach. This study aims to compare a low-intensity mindfulness intervention for the treatment of depression in PC using different intervention formats – a face-to-face MBI delivered in a group and the same MBI individually applied on the Internet – to a control group that will receive PC medical treatment as usual.

**Methods:**

A randomized controlled clinical trial will be conducted in PC, with about 120 depressed patients allocated (1:1:1) to three groups: “face-to-face MBI + TAU”, “Internet-delivered MBI + TAU”, and “TAU alone”. The MBI programs will be composed of four modules. The primary outcome will be depressive symptoms, measured through the Beck Depression Inventory, assessed at pre- and post-treatment and 6- and 12-month follow-ups. Other outcomes will be mindfulness, happiness, affectivity, quality of life, and the use of healthcare services. Intention-to-treat analysis using linear mixed models adjusted for baseline scores and routine sociodemographic analysis that could show baseline differences will be conducted. Per-protocol secondary outcome analyses will also be performed.

**Discussion:**

This is the first Spanish RCT to apply a low-intensity face-to-face MBI (plus TAU) to treat depression in PC settings compared to TAU (alone). Moreover, this study will also make it possible to evaluate the same MBI program (plus TAU), but Internet-delivered, considering their cost-effectiveness. Positive results from this RCT might have an important impact on mental health settings, helping to decrease the overload of the system and offering treatment alternatives beyond antidepressant medication through high-quality, flexible PC interventions.

**Trial registration:**

Clinical Trials.gov NCT03034343. Trial Registration date 24 January 2017, retrospectively registered.

## Background

Major Depression is a common mental disorder that produces great functional and social impairment all over the world. It is characterized by sustained states of negative affectivity and diminished positive affectivity. According to the World Health Organization (WHO), in 2020, this disorder will be the second most important cause of disability [1]. It has been estimated that around 14.0% of the European population have suffered from a lifetime history of major depressive disorder [2]. Specifically in Primary Care (PC) settings, a meta-analysis reviewing its prevalence in more than ten countries showed that the overall prevalence of depression was 19.5% [3]. In the Spanish population, prevalence rates of 29.0% have been observed for major depressive disorder and 14.6% for dysthymia in PC services [4].

Although previous studies have reported that a combination of psychotherapy and pharmacotherapy is the best treatment option [5], the usual intervention in PC settings is pharmacotherapy alone, even though it produces high relapse rates [6, 7] that increase with each depressive episode [8]. Some patients prefer psychotherapy to pharmacological treatment [9], but it should be noted that Spanish specialized services are overloaded. Moreover, it is difficult to introduce psychotherapy in PC due to problems such as the professionals’ training, high costs or work overload, professionals’ attitudes and organization, geographical and logistic difficulties, and, especially, lack of time [10]. All these problems reveal the need to offer new forms of treatment for depression in PC, and low-intensity interventions seem to be a promising solution.

On the one hand, interventions that are considered low intensity are either not guided (e.g. self-help) by highly qualified facilitators, or they are guided by highly qualified facilitators for only a short time [11]. On the other hand, brief interventions have been operationalized as consisting of more than two and less than ten appointments [12]. Although brief psychotherapies for depression are an alternative that has already been shown to be effective [13], a systematic review of low-intensity psychological interventions for depression revealed the need for more studies [9]. Mindfulness-based interventions (MBIs) have demonstrated their effectiveness in the treatment and prevention of relapse or recurrence of depression. Specifically, Mindfulness-Based Cognitive Therapy (MBCT), an intervention that combines mindfulness training and elements of cognitive therapy [14], has shown significant effects in patients with diagnostic levels of depression. In fact, NICE guidelines recommend it as the treatment of choice for depression recurrence [15]. Although there is no agreement on this topic, many authors believe that MBIs included under the umbrella of “third wave” cognitive behavioral therapy can be considered low intensity interventions. Some studies have demonstrated beneficial effects of brief mindfulness-based interventions in non-clinical populations [16–19].

In addition, internet-based treatments have been found to be promising for numerous mental health problems, including depressive symptoms [20], and for increasing the dissemination of evidence-based treatments [21]. The main advantages of these types of programs are that they reduce the contact time between the patient and the clinician, and they reach patients who would not otherwise receive treatment or are geographically distant. In addition, receiving treatment at home ensures confidentiality, minimizes stigma, and reduces the difficulty some people have when receiving psychological treatment [21]. Several systematic reviews have shown that Internet-based treatments based on Cognitive Behavioral Therapy (CBT) are effective, acceptable, and practical for the treatment of health problems such as anxiety and depressive disorders [22–25]. Furthermore, even self-guided online psychological treatments for depressive symptoms have been found to produce higher effect sizes compared to control groups [22], and in general, online treatments seem to be as efficacious as face-to-face treatment as usual for depression [5, 26, 27]. In the case of mindfulness, some studies have applied MBIs over the Internet with good results [28–30], but a literature review and meta-analysis have shown that, although online MBIs have significant effects on improving mental health, these effects could be small to moderate. Moreover, both studies concluded that more research is needed using more rigorous methods and examining long-term effects and moderators of online MBIs [27, 31].

Therefore, due to the need for further research about the possible benefits of low intensity interventions in PC settings and brief MBI applications, this study aims to compare a low-intensity mindfulness intervention for the treatment of depression in PC using different intervention formats – a face-to-face MBI in a group format (6-8 people/group) and the same MBI but individually applied on the Internet – to a control group receiving PC medical treatment as usual (TAU). The cost-effectiveness of the intervention formats, compared to TAU, is also evaluated.

The main hypothesis is that the MBI programs (face-to-face and online) will be more effective than TAU. Furthermore, improvements are also expected in secondary outcome measures (depression, positive and negative affect, and happiness) and other measures (health-related quality of life, mindfulness skills) in both intervention groups, compared to the TAU group. Additionally, the differences between face-to-face and online formats will be explored because, to our knowledge, there are no studies to date that compare MBIs applied online vs. face-to-face in this population. Finally, regarding cost-effectiveness, we expect that both MBI interventions will be more cost-effective than TAU. Additionally, cost-effectiveness differences between face-to-face and online formats will be explored.

## Methods

### Study design

Participants will be randomly allocated to a three-armed randomized controlled clinical trial with three conditions: a) “face-to-face MBI + TAU”, b) “Internet-delivered MBI + TAU”, and c) “TAU alone”. They will be assessed at pre- and post-treatment and 6- and 12-month follow-ups. The study flowchart is shown in Fig. 1. The study is currently in progress in the data recruitment stage.

**Fig. 1 Fig1:**
[figure not shown]
Flowchart of the study

This study will follow the CONSORT statement (Consolidated Standards of Reporting Trials, http://www.consort-statement.org) [32] and the SPIRIT guidelines (Standard Protocol Items: Recommendations for Intervention Trials) [33]. The study’s trial registration number is *ClinicalTrials.gov* NCT03034343.

### Ethics

This study will be conducted according to the international standards of the Declaration of Helsinki and subsequent amendments. This trial will be performed in compliance with the study protocol and with good clinical practice guidelines with the main aim of protecting and preserving human rights [34]. Data security will be guaranteed, the participants included in the study will be protected by the Organic Law on Protection of Personal Data (15/1999 of December 13, LOPD) and all relevant EU legislation in this regard, and international privacy agreements will be observed and respected. The Internet platform will be accessed through a unique username + password combination. An advanced encryption standard will be used to protect the data (AES-256). The study has been approved by the Ethics Committee of Universitat Jaume I (Castellón, Spain) and the Ethics Committee of Aragón (Zaragoza, Spain). An informed consent form will be signed by participants before randomization. Participants allocated to the TAU arm will also be offered the possibility of receiving the psychotherapy program through the format they prefer with all the contents and materials at the end of the study.

### Study population, recruitment, and eligibility criteria

This randomized controlled clinical trial will be conducted from the Health Center of Arrabal in Zaragoza (Spain). Participants will be adult PC outpatients attended to by their corresponding General Practitioners (GP), and they will be recruited by GPs working in the different Health Centers in Zaragoza (Spain). The researchers who manage the study will go to the different Health Centers to explain the study and eligibility criteria to the GPs, and they will give them an information sheet containing the study characteristics.

When a GP identifies a potential patient, s/he will explain the study to him/her and inform him/her that s/he can refuse to participate or withdraw from the study at any time, without any negative effects on their professional relationship or on future treatments that might be offered to the participant in PC. If the patient is interested, s/he will have to come to the Arrabal Health Center to clarify any doubts about the study and sign an informed consent form. Then, the patient will undergo a clinical interview and fill out the paper-and-pencil screening survey describing his/her sociodemographic and clinical characteristics. This first data collection and screening will be performed by specially trained psychologists with the objective of assessing whether the participants meet the eligibility criteria to participate in the study. If the participant meets the inclusion criteria, an independent researcher will implement randomization by telephone to avoid predictability.

Inclusion criteria will be as follows: a) older than 18 years; b) DSM-5 diagnosis of Major Depression or Dysthymia or mild or moderate depression, expressed as a score between 5 and 14 on the Patient Health Questionnaire (PHQ) [35]; c) depressive symptoms present for at least 2 months; d) having a computer and Internet at home; e) being able to read and understand the Spanish language; and f) willingness to participate in the study and sign the written informed consent form.

Exclusion criteria include: a) any diagnosis of a disease that may affect the central nervous system (brain pathology, traumatic brain injury, or dementia); b) other psychiatric diagnoses or acute psychiatric illnesses (severe range of depression, substance dependence or abuse, history of schizophrenia or other psychotic disorders, and eating disorders), except for anxious pathology or personality disorders; c) any medical, infectious, or degenerative disease that may affect mood, presence of delusional ideas, or hallucinations consistent or not with mood and suicide risk. Participants in both the TAU group and the MBI conditions can continue their medication (mainly anxiolytics and antidepressants) if there are no increases, unless they are necessary. However, they will not be allowed to receive any other psychological treatment during the study period (unless it is necessary for ethical reasons and it benefits the participant). Cases where the medication is increased or another psychological treatment is needed will be excluded from the analysis.

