#### Treatment as usual (TAU)

Participants in the treatment as usual (TAU) arm will continue to be treated by their GPs in their corresponding health centers. The treatments offered by the GPs are mainly pharmacological, with antidepressants and/or anxiolytics being the most frequent medications. In cases of suicide risk or other severe symptoms or unexpected effects during the study, the patient will be referred to specialized mental health care services and excluded from the data analysis.

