### Main analysis

The efficacy of the “face-to-face MBI + TAU” group compared to the “TAU alone” group will be estimated based on the main BDI-II outcome, which will be considered a continuous variable. Multilevel mixed-effects models will be developed by means of a RM design on an intention-to-treat (ITT) basis, using the restricted maximum likelihood (REML) method, in order to produce unbiased estimates of variance/covariance parameters [54]. Non-standardized slopes and 95% confidence intervals (95% CI) will be calculated by adjusting those variables that show significant differences between groups at baseline. In order to study the specific trajectories of each group throughout the trial and determine whether possible differences between groups are consistent over time, the ‘group x time’ interactions will be calculated. Cohen’s d effect sizes will be calculated at each time point using the combined standard deviation at baseline [64]. Effect sizes are small when d ≤ 0.2; medium when d = 0.5; and large when d ≥ 0.8 [65].

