### Secondary analysis

The efficacy of the “face-to-face MBI + TAU” group compared to the “TAU alone” group with regard to the secondary outcomes and the other measures, and the efficacy of the “Internet-delivered MBI + TAU” compared to the “TAU alone”, as well as the exploratory comparison of the “face-to-face MBI + TAU” and “Internet-delivered MBI + TAU” on the primary and secondary outcomes, will be calculated following the same analytical strategy used for the main analysis. Per protocol analysis will also be performed, considering only those patients who attend at least 3 modules (out of 4). The clinical significance of improvements between groups will be explored by calculating the absolute risk reduction and number needed to treat (NNT) (and their 95% CI). We will use two criteria for improvement: a) changing to a less severe cluster in the BDI-II compared to the one the patient was allocated to at baseline; c) calculating the clinical significance of improvements by establishing both the cut-off point and reliable change index on the BDI-II total score using the Jacobson and Truax method [66]. Additionally, possible differences in PHQ-9 and PANAS will be explored throughout the MBI modules using mixed models.

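### Two rules exclude randomised patients from the analysis because of events after randomisation, which contradicts the intention-to-treat main analysis and can bias the BDI-II comparison in either direction

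*Protocol article*

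**What the plan says.** Four places in the protocol article bear on who is analysed.

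- **Study population, recruitment, and eligibility criteria.** Patients in all conditions may stay on their drugs: "Participants in both the TAU group and the MBI conditions can continue their medication (mainly anxiolytics and antidepressants) if there are no increases", with an exception where an increase is necessary. Other psychological treatment is barred, again with an exception for need. The section then states: "Cases where the medication is increased or another psychological treatment is needed will be excluded from the analysis".
- **Treatment as usual (TAU).** For anyone who develops suicidality, marked worsening or an unforeseen reaction while in the trial, the rule is: "the patient will be referred to specialized mental health care services and excluded from the data analysis". The sentence stands under the TAU heading and does not say whether it also covers the two mindfulness arms.
- **Main analysis.** "Multilevel mixed-effects models will be developed by means of a RM design on an intention-to-treat (ITT) basis". The abstract's Methods paragraph says the same: "Intention-to-treat analysis using linear mixed models adjusted for baseline scores".
- **Secondary analysis.** A per-protocol analysis is added, restricted to patients who attended at least three of the four modules. Medication changes, added therapy and referral play no part in that definition.

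The sample size section inflates 33 per group to 40 per arm for an expected dropout of about 20%. It does not mention the exclusions.

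**The concern.** An ITT analysis compares the groups as randomised. Removing a patient because of something that happened during the trial breaks that comparison, and these particular events are not neutral. A medication increase, a need for other psychological help, or a referral for suicide risk or severe symptoms plausibly marks a patient who is getting worse. Removal would then be linked to the BDI-II.

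Nor need the events be equally frequent across arms. The comparator is GP care, of which the protocol says: "The treatments offered by the GPs are mainly pharmacological, with antidepressants and/or anxiolytics being the most frequent medications". If the mindfulness programme works, fewer patients in those arms should need escalation. If the suicide-risk rule applies only to TAU, where it is printed, the selection is unequal by design.

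At stake is the primary estimate. It could be pulled towards zero if TAU loses more of its worst cases, or inflated if a mindfulness arm does.

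**Working it through.** **1. Can the texts be reconciled?**

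- *Timing.* The first rule concerns patients already in the TAU and mindfulness conditions; the second concerns events during the study. Both therefore act after randomisation.
- *Scope.* Neither rule is limited to a sensitivity or per-protocol analysis.
- *Per-protocol set.* It is defined by attendance alone, so the exclusions cannot be read as part of it.

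No reading leaves both the exclusions and the ITT label intact.

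**2. The plan's own figure.** For two means with difference 3.5, SD 5, two-sided 5% and 80% power:

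n = 2 × (1.960 + 0.842)² × 5² / 3.5² = 2 × 7.85 × 2.041 ≈ 32.04, rounded up to 33 per group.

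This agrees with the stated 33. A repeated-measures F test with the protocol's means and correlations gives 32 or 33, depending on the visit spacing assumed. The planning arithmetic is not the problem; the analysis population is.

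**3. How far could the estimate move?**

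Inputs from the sample size section: post-test means 19.5 (TAU) and 16 (face-to-face), SD 5, true effect 3.5. Assumptions, because the protocol gives no values: the proportion p excluded in each arm, and the correlation r between the exclusion trigger and post-test BDI-II.

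If the top proportion p on a normally distributed trigger is removed, the mean of those kept falls by r × 5 × λ(p), where λ(p) = φ(z) / (1 − p) and z is the (1 − p) normal quantile:

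- λ(0.10) = 0.1755 / 0.90 = 0.195
- λ(0.20) = 0.2800 / 0.80 = 0.350
- λ(0.30) = 0.3477 / 0.70 = 0.497

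Expected difference = 3.5 − 5r × [λ(TAU) − λ(face-to-face)].

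| Excluded, TAU vs face-to-face | λ difference | r = 0.2 | r = 0.3 | r = 0.5 | r = 0.7 |
|---|---|---|---|---|---|
| 20% vs 10% | 0.155 | 3.35 | 3.27 | 3.11 | 2.96 |
| 30% vs 10% | 0.302 | 3.20 | 3.05 | 2.75 | 2.44 |
| 10% vs 20% | −0.155 | 3.65 | 3.73 | 3.89 | 4.04 |
| equal | 0 | 3.50 | 3.50 | 3.50 | 3.50 |

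Example, first row, r = 0.5: 3.5 − 5 × 0.5 × 0.155 = 3.11.

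The shift does not depend on the true effect. With no true effect, 20% vs 10% at r = 0.5 would give a spurious difference of about 0.39 points favouring TAU.

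**4. One severity threshold applied alike to both arms.** This need not remove equal proportions. If the threshold excludes 20% of TAU and r = 0.5, the face-to-face trigger mean lies 0.5 × 0.7 = 0.35 SD lower, so the cut-off there is z = 0.842 + 0.35 = 1.192. That excludes 11.7% of face-to-face patients, with λ = 0.1961 / 0.8833 = 0.222. The expected difference is 3.5 − 2.5 × (0.350 − 0.222) = 3.18. A rule applied evenly can therefore still shrink a true effect.

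**The case against.** **Bias is possible, not shown.** The protocol gives no exclusion rate, no difference between arms and no link between trigger and outcome. Equal proportions removed leave the difference at 3.5. This stands, and it is why the size and direction are left open. The case in step 4 of the working shows only that an evenly applied rule does not guarantee equal proportions.

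**The correlation may be weak.** The primary outcome is BDI-II at post-test, six weeks after baseline for face-to-face and TAU, while the rules run through the 12-month follow-up. Later triggers would plausibly relate less to the six-week score. This also stands, and the range therefore starts at 0.2.

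**GPs are said to be blind.** They manage the medication, which weakens any argument that mindfulness patients are watched more closely for drug increases. Fair; the direction cannot be settled by argument.

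**Stronger readings a reader might infer, which the text does not support:**

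- *That the trial loses a stated amount of power.* An unadjusted post-test comparison starting from 33 per arm gives about 67% power for 20% vs 10% excluded. The plan is a mixed model adjusted for baseline scores, and an approximate adjustment for a baseline correlation of 0.6 gives about 85%. No power figure is claimed here.
- *That the sample falls below the 20% allowance.* The protocol does not say whether that allowance includes these exclusions.
- *That the excluded patients vanish from the report.* They are excluded from analysis; CONSORT reporting is promised, and nothing says their numbers will be withheld.
- *That TAU inherently includes drug increases.* The text says only that TAU is mainly pharmacological.

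None of these points removes the contradiction between the exclusion rules and the ITT label.

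**Conclusion.** The point holds as a contradiction about the analysis population. The protocol promises an ITT main analysis and also instructs that randomised patients be excluded for post-randomisation events plausibly tied to worsening. Whether the suicide-risk rule applies to all arms is itself unclear. It must be resolved before analysis because it decides who enters the primary comparison.

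The effect on the estimate is of unknown size and can go either way. Under the assumed rates and correlations (0.2 to 0.7), a true 3.5-point effect would appear as roughly 2.4 to 3.35 points if TAU loses more patients, and roughly 3.7 to 4.0 if face-to-face loses more. It would not move if equal proportions were removed. These figures illustrate a post-test difference in means; they do not predict the result of the planned mixed model.

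**What to change.** For the main analysis, delete both exclusion rules. State that every randomised patient's available BDI-II data enter the ITT mixed model whatever the medication change, added therapy or referral (a treatment-policy handling of these events). State that scheduled assessments continue after such an event where the patient agrees. Report the number of each type of event by arm. If the analysis without these patients is still wanted, keep it as a labelled sensitivity analysis and say which arms each rule covers.

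The cost is a few sentences of wording. There is also continued questionnaire follow-up if assessments now stop after such an event, which the document does not say. The trial was already recruiting when the protocol was published, so data missed so far may be unrecoverable; that should be reported. The change concerns the analysis only and leaves the clinical handling of these patients as it is.
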